### Intervention and control

#### Intervention

All participants will receive nutritional counseling by a bariatric dietitian as a routine standard of care, which includes strictly fluid diet for the first months. (Additional file 1).Before discharge from the hospital, patients will be provided with the supplement and will be advised by the dietitian regarding its use (one can per day, over 3–5 intervals, i.e. the bottle will be used over the entire course of the day through a number between 3 and 5 shots/doses).Each supplement (bottle) contains 20 g of protein, 250Kacl plus different micronutrient and macronutrient, per 200 ml can (Cubitan,Protein, Nutricia, Netherlands) (Additional file 2).

#### Control (placebo)

All participants will receive nutritional counseling by a bariatric dietitian as a routine standard of care, which includes strictly fluid diet for the first months. (Additional file 2).Before discharge from the hospital, patients will be provided with the supplement (placebo) and will be advised by the dietitian regarding its use (one can per day over 3–5 intervals).Following hospital discharge, Control patients will receive supplement that contains 0 g protein, fat free, 100 kcal and enriched with electrolytes per 200 ml can (preOp, Nutricia, Netherlands) (Additional file 2).

*Note: Both groups will be instructed to take one supplement pack through the day in equally divided portions, and, they should store it in room temperature and drink it without heating.

#### Materials

The protein supplement, a familiar treatment option at HMC, consists of whey protein isolate with the following characteristics:Pure Whey Protein Isolate.Whey protein isolate is the most pure and concentrated form of whey protein available.Whey protein isolate contains higher protein content (90–95%) and less lactose (<0.5%). It is a complete protein with all the indispensable essential amino acids and is an exceptional source of branch chain amino acids (BCAAs), especially leucine, necessary for tissue growth.Whey protein is a soluble, easy to digest protein and is efficiently absorbed into the body (Marshall, 2004).Aside from amino acids, other biological components of whey protein include lactoferin (concentration is commonly 0.35–2.0% of total proteins), immunoglobulins (10–15% of total whey proteins), lactoperoxidase (accounts for 0.25–0.5% of total protein in whey), glycomacropeptide (with 10–15%), and bovine serum albumin (10–15% of total whey protein). These bioactive components together with the essential and non-essential amino acids help improve body mass index especially in individuals doing exercise programs, by enhancing muscle mass and reducing fat mass. (Marshall, 2004).A 200 ml intervention can contains 20 g of protein, 250Kacl plus various micronutrient and macronutrient.A 200 ml placebo can contains 0 g protein, fat free, 100 kcal and enriched with electrolytes, per can (200 ml).

#### Measurements

Baseline measurement of body composition (fat mass and muscle mass), height and weight will be conducted on day one of the trial, using Tanita body composition instrument and other physical body measures.Baseline blood test for total protein, albumin, Vit B12, Zinc and Magnesium levels will be collected.All of the above measurements will be repeated at 1 month, 3 months and at the end of the follow up period (6 month).

*Note: All of the above measurements and the collection of blood sample is routine practice for post-bariatric surgery patient.

#### Study visits

Patients follow up visit once every month post-surgery at the Bariatric Dietician Clinic in OPD department at HGH, and covers the following:A.Post-surgery dietary advice, to sustain a hypo caloric and protein-rich diet.B.Anthropometric parameters for body composition (see below).C.All patients will be followed up through weekly phone calls to ensure compliance and adherence to the study protocol. Questions such as “how many bottles of supplements are left?” Or, “how many bottles have you had so far?” will be asked. Patients will be asked to use a diary to register their daily use of the products as well as fill the forms provided by the hospital in relation to consumption of supplement.D.Collection of blood sample will take place following an overnight fasting. All blood markers will be measured and calculated in the central laboratory at HGH.

#### Body composition (BC)

The measurements of anthropometric data will be done following overnight fast with patients wearing light clothes and barefoot (baseline and follow up). Tanita’s body composition analyzer used for body composition measurements provides precision in estimating body Weight, Body Fat Percentage, Body Fat Mass, Body Mass Index (BMI), Fat Free Mass, and Estimated Muscle Mass and percentage. Height will be measured using a fixed wall stadiometer. Both inter- and intra-reliability testing on all measures, including TanitaHealthWare, are conducted prior to the trial to ensure consistency of the measures across the study population. This is a standard hospital procedure and these tests will ensure that the assessment tools produced are consistent and reliable measurements.

#### Blood sample

Blood samples will be collected from patients in (HGH) laboratory at baseline and every month thereafter following an overnight fast. Complete blood count (CBC) will be used. Total protein, serum Albumin, zinc, magnesium and vitamin B12 will also be assessed. The laboratories of HGH are internationally accredited laboratories that follow international standards.

#### Data collection and handling

All data obtained from this study will be collected by the principal investigator and will be saved in a secure location where only the project supervisors and a statistician will be able to access. Data will be de-identified during and post collection period to ensure privacy and ethical protocols are maintained. All data will be stored and kept safe for a period of time according to HMC policy and will remain a property of HMC. The actual physical location of all electronic copies will also be at HGH. Confidentiality of patients will be highly maintained throughout the trial.

#### Study timeline

All participants will be followed up for 3 and 6 months from day one of their participation. Therefore, each randomized pair will have their own follow-up dates, based on the recruitment pattern at the HGH. For example, a patient who enters the trial on the 3rd May, he or she will have the 3 months follow up date on the 3rd August and the 6th months follow up date on the 3rd November.

## Statistical analysis

Data analyses will be performed using the statistical software SPSS package 23. The main aim is to analyze Body composition and other anthropometric changes throughout the follow up. The normality of the variables will be assessed by the Kolmogorov-Smirnov test. Non-parametric tests will be used in case of non-normal distributions of variables. Characteristics and demographics of participants will be summarized, based on the assignment of treatment or placebo, using means and standard deviations (SD) for quantitative variables. Baseline data for the two groups will be compared using two tailed independent samples t-tests and the *P* value of this difference for each variable will be provided. During the follow-up, changes in weight, body fat percentage, muscle mass, total protein level, albumin level, vit B12, Zinc and Magnesium will be compared within groups using paired t-test and between groups using independent sample t-test. In the case of non-normal distribution of variables, any two independent (unpaired) samples Student’s t test will be replaced by Mann-Whitney U test. However, in the case of Two dependent (paired) samples Student’s t test, Wilcoxon signed rank (paired samples) test will be used. A multiple linear regression model will also be conducted to adjust for age and gender will be conducted. Other fundamental confounders such as diet intake are not incorporated into the multiple binary regression model. This is primarily because post-bariatric patients within the 1st few months (early post-operative phase) are both unable and not allowed to take any solid foods and few specific liquid foods such as milk and soups are recommended to them by the dietician. All patients are trained to follow such diet. Moreover, being an RCT, it is expected that all confounders (including hidden confounders) are balanced between the 2 groups and no assessment of baseline variables such as diet, physical activity and any other biological differences between the 2 groups is required. This is consistent with the CONSORT statement for RCTs.

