### Study objectives

#### Primary objective

To estimate the difference in change of muscle and fat mass between participants who received protein supplement and those who received the placebo.

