### Sample size

The study population are bariatric patients admitted to bariatric department for surgery based on their eligibility criteria (BMI ≥ 35). All patients will be enrolled in the study prior to admission and will be given the intervention or the placebo on the first day post-surgery, depending on their randomization. A total of 160 obese Qatari adults from Bariatric and Metabolic Center in Hamad General Hospital (HGH), who fulfill HGH entry criteria for bariatric surgery, are expected to be enrolled in this experimental study.

Using the primary outcome estimates available in the published study (Schollenberger, A E et al.; 2016), body fat mass (BFM) and lean body mass (LBM) (kg) in the intervention group at baseline, 3 and 6 months (BFM baseline 78.2 ± 19.1, 3 and 6 months 59.9 ± 15) and (LBM baseline 65.2 ± 14.2, 3 and 6 months 58.2 ± 10.6) compared with Placebo group (BFM baseline 68.2 ± 12.0, 3 and 6 months 53.9 ± 11.5) and (LBM baseline 68.9 ± 13.4, 3 and 6 months 62.2 ± 11.3). Considering a 90% power and a type I error rate of 5%, the required sample size would be 130 participants (65 in each group), however, to compensate for possible dropouts, non-compliance and loss to follow-up an additional 15% to 20% will be added to the above sample size (a total of 160 participants i.e., 80 in each group). The only difference between the above study population and the population of our RCT is that the German study population were more obese (BMI between 49 and 52). Both studies looked at the effect of protein supplementation on muscle and fat mass in post-bariatric surgery patients.

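### The primary objective and sample size use fat mass, but the Statistical analysis section lists body fat percentage for testing and omits fat mass

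*Protocol article*

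**What the plan says.** The Primary objective reads: "To estimate the difference in change of muscle and fat mass between participants who received protein supplement and those who received the placebo". It has two outcomes and gives no unit.

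Fat mass is also the quantity in the abstract (measured at every visit, and named in the hypothesis under Strengths and limitations) and in Measurements, where body composition is spelled out as fat mass and muscle mass. Sample size takes its primary outcome estimates as "body fat mass (BFM) and lean body mass (LBM) (kg) in the intervention group at baseline, 3 and 6 months", with matching figures for placebo.

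The Statistical analysis section opens broadly: "The main aim is to analyze Body composition and other anthropometric changes throughout the follow up". It then lists what is tested: "changes in weight, body fat percentage, muscle mass, total protein level, albumin level, vit B12, Zinc and Magnesium will be compared within groups" by paired t-test and "between groups using independent sample t-test". Body fat percentage is on the list; fat mass is not. The regression adjusting for age and gender names no outcome.

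The Body composition section shows that the analyser reports these as distinct quantities: "Body Fat Percentage, Body Fat Mass, Body Mass Index (BMI), Fat Free Mass, and Estimated Muscle Mass".

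**The concern.** The only section that assigns tests to named variables departs from the objective on one of its two outcomes. Body fat percentage is fat mass divided by total weight. It changes when fat changes, but also when lean mass changes, and lean mass is the other half of the primary objective. A supplement that preserved lean mass and left fat mass untouched would lower body fat percentage, and the result could be read as a fat benefit.

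Two things are at stake. If the list is followed, the fat result answers a different question from the one in the objective, on a variable for which the sample size gives no planning figures. If the list is not followed, the document leaves two candidate fat measures, and the choice could be made after the data are seen.

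**Working it through.** **1. Which variable each section uses**

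| Section | Fat outcome | Lean outcome |
|---|---|---|
| Abstract | fat mass | muscle mass |
| Primary objective | fat mass | muscle mass |
| Sample size (planning figures) | body fat mass, kg | lean body mass, kg |
| Measurements | fat mass | muscle mass |
| Statistical analysis (test list) | body fat percentage | muscle mass |

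The test list is the odd one out on fat. Sample size is the odd one out on lean mass.

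**2. The plan's own figure**

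Sample size states 65 per arm (90% power, 5% type I error) but does not say which comparison gives it. Take n per arm = 2(z₀.₉₇₅ + z₀.₉₀)² SD²/d², two-sided, with SD the root mean square of the two follow-up SDs:
- Fat mass at follow-up: d = 59.9 − 53.9 = 6.0 kg, SD = √((15² + 11.5²)/2) = 13.37, n = 105.
- Lean mass at follow-up: d = 62.2 − 58.2 = 4.0 kg, SD = √((10.6² + 11.3²)/2) = 10.96, n = 158.

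Neither gives 65. That is a separate matter. It means only that the stated size cannot be used to infer which fat measure was intended. No percentage appears among the inputs.

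**3. The same planning means as mass and as percentage**

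Assume weight = fat mass + lean mass, and use ratios of group means, since individual data are not given. Percentage = fat/(fat + lean).
- Intervention: 78.2/143.4 = 54.53%, then 59.9/118.1 = 50.72%, a change of −3.81 points.
- Placebo: 68.2/137.1 = 49.74%, then 53.9/116.1 = 46.43%, a change of −3.32 points.
- Difference in change: about 0.5 percentage points.
- Fat mass: (78.2 − 59.9) − (68.2 − 53.9) = 18.3 − 14.3 = 4.0 kg.

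The two measures are not interchangeable. The figures are in different units and do not rank the measures.

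**4. How far percentage moves with no change in fat**

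Hold fat at 53.9 kg and start from lean mass 62.2 kg (placebo follow-up). The lean mass saved is an assumption, shown over a range:
- 0 kg: 53.9/116.1 = 46.43%
- 1 kg: 53.9/117.1 = 46.03% (−0.40)
- 2 kg: 53.9/118.1 = 45.64% (−0.79)
- 3 kg: 53.9/119.1 = 45.26% (−1.17)

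This is about 0.4 points per kilogram of lean mass, with no fat lost.

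**The case against.** The strongest reply is that fat mass does have an analysis. The abstract says it is measured at every visit and that the study variables will be compared between groups by t-test. The Statistical analysis section announces body composition as its aim, and Measurements defines that as fat mass and muscle mass. On this reading the list is a slip. This stands to the extent that a reader who inferred that fat mass is never analysed would go too far. It does not remove the fault: a general phrase does not override a list that names a different variable, and the document still leaves the fat measure open.

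A reader might also infer that both primary outcomes are displaced. They are not, because muscle mass is on the test list. Nor does the sample size rest on lean mass alone: it quotes both fat and lean mass.

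The move from 4.0 kg to 0.5 points might be taken as a loss of effect or power. The document gives no SD of change for either measure, so no such loss can be shown. A lean-mass benefit counted twice is likewise only a possibility. The planning means show lean loss of 65.2 − 58.2 = 7.0 kg with intervention and 68.9 − 62.2 = 6.7 kg with placebo, which is no lean saving.

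Finally, the Background itself raises a higher fat percentage as a worry, so the percentage is a reasonable variable to report. That supports keeping it, but not letting it replace fat mass.

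**Conclusion.** The point holds for the fat half of the primary objective. The objective, the abstract, Measurements and Sample size use fat mass. The list of tested variables uses body fat percentage, a different device output that depends on lean mass. As written, the named test does not match the objective or the variable used for planning.

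The size of the discrepancy is about 0.4 percentage points for each kilogram of lean mass at the placebo planning means, with fat unchanged. This rests on weight being the sum of fat and lean mass, and on an assumed lean saving that the planning figures do not themselves show. The defect does not depend on that illustration; it follows from setting the sections side by side.

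The use of lean body mass in Sample size is a minor labelling matter. It is a published planning estimate, and the section itself describes both studies as concerned with muscle and fat mass. Because the analyser reports fat free mass and estimated muscle mass separately, the link should still be stated.

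**What to change.** In Statistical analysis, name change in fat mass (kg) beside change in muscle mass as the primary outcomes for the between-group test. Keep body fat percentage, if wanted, as an additional variable marked non-primary; how it is labelled beyond that is the authors' choice.

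In Sample size, add a sentence saying that lean body mass is used as a planning proxy for muscle mass.

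The cost is wording only: the analyser already records every quantity, and no visit or measurement is added. The change should be made before any comparison by arm. If body fat percentage was in fact meant to be primary, the objective and the sample size would have to change instead, with planning figures for the percentage that the document does not contain.

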**Methods and analysis:**

The study was based at the Department of bariatric and metabolic surgery, Doha metropolitan and regional areas. It is envisaged that approximately 160 post-bariatric surgery patients will be randomized and followed up for 6 months. These will be males and females obese (BMI >35) Qatari patients between the aged 18–60 years. Subjects with renal or liver disease and those with past history of bariatric surgery will be excluded. By the completion of the trial, patients who took less than 80% of the supplement will be further excluded from the final analysis. Protein supplement (Cubitan,Protein, Nutricia, Netherlands) that contain daily intake of 20 g of protein to be taken orally 3 times a day throughout the study period. The placebo group will receive identical ampule containing zero-protein with exact instructions as per the intervention group. Body weight, muscle and fat mass, total protein, albumin, vit B12, Magnesium and Zinc will be measured at baseline and every follow up/study visit. Study variables will be compared between the 2 groups at different stages of the trial, including baseline, using Sample T-test (paired and unpaired) and the significance level will be confirmed with the 95% confidence interval with alpha error set to 0.05.

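### Within-arm paired tests are planned beside the between-arm tests without saying which supports the treatment conclusion, and the abstract names a paired test for comparing two unmatched groups (minor)

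*Protocol article*

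**What the plan says.** The Statistical analysis section lists changes in weight, body fat percentage, muscle mass, total protein, albumin, vitamin B12, zinc and magnesium. These are to be "compared within groups using paired t-test and between groups using independent sample t-test". For non-normal data the paired test has its own replacement: "Wilcoxon signed rank (paired samples) test will be used". The within-arm comparisons are therefore planned as significance tests and not only as summaries. The section then adds: "A multiple linear regression model will also be conducted to adjust for age and gender". The baseline value of the outcome is not among the covariates.

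The abstract (Methods and analysis) condenses this to: "Study variables will be compared between the 2 groups at different stages of the trial, including baseline, using Sample T-test (paired and unpaired". Read literally, that puts the paired test under the comparison of the two groups.

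The Primary objective is a between-arm quantity: "To estimate the difference in change of muscle and fat mass between participants who received protein supplement and those who received the placebo". The first three Secondary objectives also set intervention against control. Methods and design describes random allocation of individual patients, with no matching.

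**The concern.** A paired test within one arm asks whether that arm changed from baseline. After bariatric surgery the answer for body composition is yes in both arms, whether or not protein was given. Such a result says nothing about the supplement, yet the plan sets these tests beside the between-arm tests and does not rank them.

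Where the change within each arm is small, as it might be for a blood marker, the hazard is different. One arm may cross the 5% line and the other miss it by chance, and that contrast is easily taken for an effect. It is not a test of the difference between arms and does not hold the 5% error rate.

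The abstract's wording is a separate slip. A paired test needs matched observations, and patients in the two arms are not matched.

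**Working it through.** **Inputs from the Sample size section (figures of the cited study).**
- Fat mass, kg: intervention 78.2 (SD 19.1) to 59.9 (SD 15), change −18.3; placebo 68.2 (SD 12.0) to 53.9 (SD 11.5), change −14.3.
- Lean mass, kg: intervention 65.2 (SD 14.2) to 58.2 (SD 10.6), change −7.0; placebo 68.9 (SD 13.4) to 62.2 (SD 11.3), change −6.7.
- 65 evaluable per arm; alpha 0.05, taken as two-sided.

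The plan states no figure for the within-arm tests, so there is none to reproduce. The 65 per arm is taken as given. It does not follow from the stated inputs alone (follow-up fat mass, two-sided, 90% power, gives 105 per arm), but that is a separate matter and nothing below depends on it.

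**Assumption.** The SD of change is not given. It is derived as SD² = s₀² + s₁² − 2·r·s₀·s₁, with an assumed baseline to follow-up correlation r of 0.5 to 0.95.

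**Step 1: what the within-arm tests would show.** Expected t = change / (SD/√65).
- Lean mass, placebo, r = 0.5: SD = 12.48, t = 6.7/(12.48/√65) = 4.3, power 0.99. At r = 0.95: SD = 4.42, t = 12.2, power 1.00.
- Lean mass, intervention: t = 4.4 to 10.7, power 0.99 to 1.00.
- Fat mass: t = 9.8 to 30.8 (placebo) and 8.5 to 21.9 (intervention), power 1.00 in both.
- Even at r = 0 the expected t is 3.1 for placebo lean mass: SD = √(13.4² + 11.3²) = 17.53, and 6.7/(17.53/√65) = 3.1, against a critical value of 2.0.

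The placebo arm would be significant with no protein given.

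**Step 2: one arm significant, the other not, with no supplement effect.** If both arms have the same true change and within-arm power p, the chance is 2p(1−p).
- Lean mass: about 0 to 2%, because both arms reject.
- Small changes, with the standardized size assumed because the documents give no blood-marker data:

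| Assumed change (SD units) | p at n = 65 | 2p(1−p) |
|---|---|---|
| 0.20 | 0.355 | 46% |
| 0.25 | 0.510 | 50% |
| 0.30 | 0.664 | 45% |
| 0.35 | 0.794 | 33% |
| 0.40 | 0.888 | 20% |

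In simulation with equal true changes (20,000 runs, 65 per arm), the planned between-arm t-test of change rejected in 4.9% of trials. The table is illustrative and does not apply to lean or fat mass.

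**Step 3: what adding the baseline value gains.** For lean mass, compare the variance of the change score with the residual variance after regression on baseline, s₁²(1 − r²), taken arm by arm.
- Intervention, r = 0.8: 73.17 against 112.36 × 0.36 = 40.45, a cut of 45%. At r = 0.9: 43.06 against 112.36 × 0.19 = 21.35, a cut of 50%.
- Placebo, r = 0.8: 64.98 against 127.69 × 0.36 = 45.97, a cut of 29%. At r = 0.9: 34.69 against 127.69 × 0.19 = 24.26, a cut of 30%.

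**Step 4: abstract against body text.** The Statistical analysis section assigns paired tests to within-group and independent tests to between-group comparisons. The abstract assigns both to the between-group comparison. With individual randomization only the former is coherent.

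**The case against.** The strongest reply is that the right analysis is already there. The same sentence plans an independent-samples test of change, Mann-Whitney is its fallback, a regression follows, and the objective is a difference between arms. That stands, and it keeps the point minor. A reader might infer that the plan will judge the supplement by within-arm p-values, or that it gives them equal weight. The documents do not support this: no section bases a treatment conclusion on a within-arm test, and sharing a sentence is not a ranking.

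It can also be said that describing change in each arm is legitimate, and that labelling it descriptive could sit in an analysis plan not shown. The first part is right, and a mean with its confidence interval serves that purpose. The second is possible, but the article does more than stay silent: it specifies tests and their non-parametric replacements.

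On the abstract, a reader might infer that a paired test will actually be run across the arms. The Statistical analysis section points the other way, and the abstract is best taken as a loose condensation. It is still literally wrong.

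Two limits on the numbers also stand. The planning figures are fat and lean mass in kg, while the tested list names body fat percentage and muscle mass; they are used here only to show that both arms change. The 20 to 50% figures rest on assumed effect sizes.

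**Conclusion.** The point holds as a minor one. The within-arm tests cannot show a supplement effect, the plan does not say that the between-arm comparison alone supports the conclusion, and the abstract misassigns the paired test. For body composition the within-arm tests would reject in both arms almost regardless (power about 0.99 or more at 65 per arm, r from 0.5 to 0.95), so they carry no information on treatment. For a variable with a small change, assumed 0.2 to 0.4 SD, a one-arm-only pattern would arise by chance in about 20 to 50% of trials without any supplement effect. That does harm only if someone reads the pattern as an effect, which the plan does not propose.

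The substantive gain lies in the regression. It adjusts for age and gender but not for the baseline value of the outcome, although that value is collected. On the planning SDs, and at an assumed correlation of 0.8 to 0.9, adding it would cut the lean-mass variance by about 45 to 50% in the intervention arm and about 30% in the placebo arm, compared with the change score. The unadjusted between-arm test remains valid without it.

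**What to change.** 1. In the Statistical analysis section, replace the paired t and signed-rank tests by within-arm mean change with 95% CI, described as descriptive and without a test.
2. State that every conclusion about the supplement rests on the between-arm difference from the planned linear regression, with the baseline value of the outcome added to age and gender. With baseline in the model, the treatment estimate is the same whether the response is the follow-up value or the change.
3. Reword the abstract so that no paired test is named for the between-group comparison.

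The cost is a few sentences and one covariate that is already measured at baseline. No extra data or patients are needed, and fewer tests are run. The changes should be fixed before unblinding.

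### The between-group test of change is unadjusted and can switch to Mann-Whitney; the baseline value of the outcome is subtracted but never used as a covariate, which costs precision.

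*Protocol article*

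**What the plan says.** The primary objective is "To estimate the difference in change of muscle and fat mass between participants who received protein supplement and those who received the placebo". For the follow-up data, the Statistical analysis section says that "changes in weight, body fat percentage, muscle mass, total protein level, albumin level, vit B12, Zinc and Magnesium will be compared within groups" by paired t-test and "between groups using independent sample t-test". No covariate enters that comparison.

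Two further rules apply:

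- A pre-test chooses the method: "The normality of the variables will be assessed by the Kolmogorov-Smirnov test", and "Non-parametric tests will be used in case of non-normal distributions of variables". For two independent samples, the t-test "will be replaced by Mann-Whitney U test".
- One regression is named: "A multiple linear regression model will also be conducted to adjust for age and gender". Whether its dependent variable is the change or the follow-up value is not stated.

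The Measurements section has fat mass, muscle mass, weight and the blood markers measured on day one. No section puts the baseline value of an outcome into a model. The reason given in Statistical analysis for leaving out other variables is that randomisation is expected to balance them.

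**The concern.** A change score subtracts the whole of the baseline value, as if the slope of follow-up on baseline were 1. Where the true slope is below 1, change is correlated with baseline. Two things follow. Part of the variance of change could be removed by adjusting for baseline, so the t-test is less precise than it could be at the same sample size. In addition, a chance gap between the arms at baseline carries through in part to the estimated difference in change. Expected balance does not answer this: randomisation balances arms on average, not in each single trial.

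The normality switch adds a second problem. Mann-Whitney U compares ranks and does not estimate a mean difference. If the switch is triggered, the analysis no longer delivers the quantity named in the primary objective. The method can also differ from one variable to another, depending on the data.

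**Working it through.** The plan gives no figure for the precision of this comparison, so there is none to reproduce. The planned 65 per arm is used below only as an arm size.

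**Inputs** (Sample size section, cited study, kg; for example "BFM baseline 78.2 ± 19.1" in the intervention arm)

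| | Intervention SD, baseline → follow-up | Placebo SD, baseline → follow-up | Pooled SD, baseline → follow-up |
|---|---|---|---|
| Fat mass | 19.1 → 15 | 12.0 → 11.5 | 15.95 → 13.37 |
| Lean mass | 14.2 → 10.6 | 13.4 → 11.3 | 13.81 → 10.96 |

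Pooled SD = sqrt((SD₁² + SD₀²)/2). For example, baseline fat is sqrt((19.1² + 12.0²)/2) = 15.95.

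The baseline/follow-up correlation r is not in the document. I assume 0.5 to 0.9.

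**Formulas** (s₁ = baseline SD, s₂ = follow-up SD)

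- Variance of change = s₁² + s₂² − 2·r·s₁·s₂
- ANCOVA residual variance = s₂²·(1 − r²)
- Slope b = r·s₂/s₁
- With s₁ = s₂, the variance ratio reduces to (1 + r)/2

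**Step 1: variance ratio.** Fat mass, pooled SDs, r = 0.8:

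- Change: 254.4 + 178.6 − 2 × 0.8 × 15.95 × 13.37 ≈ 92.0
- ANCOVA: 178.6 × 0.36 = 64.3
- Ratio: 64.3/92.0 = 0.70

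| ANCOVA / change-score variance | r = 0.5 | 0.7 | 0.8 | 0.9 | Reduction |
|---|---|---|---|---|---|
| Fat, pooled SDs | 0.61 | 0.68 | 0.70 | 0.69 | 30-39% |
| Fat, placebo-arm SDs | 0.72 | 0.81 | 0.86 | 0.90 | 10-28% |
| Lean, pooled SDs | 0.57 | 0.62 | 0.63 | 0.59 | 37-44% |
| Lean, placebo-arm SDs | 0.61 | 0.68 | 0.71 | 0.70 | 29-39% |
| Equal SDs at both times | 0.75 | 0.85 | 0.90 | 0.95 | 5-25% |

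In sample-size terms, ANCOVA would match the precision of a t-test of change with 65 per arm using about 65 × 0.61 = 40 to 65 × 0.70 = 45 per arm (fat, pooled SDs). With placebo-arm SDs the figures are about 65 × 0.72 = 47 to 65 × 0.90 = 59.

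**Step 2: a chance baseline gap of ordinary size.** The standard error of the baseline difference in fat mass at 65 per arm is 15.95 × sqrt(2/65) = 2.8 kg. A gap of one SE shifts the estimated difference in change by (1 − b) × 2.8 kg:

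- r = 0.5: b = 0.42, shift 0.58 × 2.8 = 1.6 kg
- r = 0.8: b = 0.67, shift 0.33 × 2.8 = 0.9 kg
- r = 0.9: b = 0.75, shift 0.25 × 2.8 = 0.7 kg

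For scale, the difference in fat-mass change in the cited study is (59.9 − 78.2) − (53.9 − 68.2) = −4.0 kg. With the placebo-arm SDs the one-SE gap is 12.0 × sqrt(2/65) = 2.1 kg and the shift is 0.3 to 1.1 kg.

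**Step 3: the test against the objective.** The primary objective asks for a difference in change, and the abstract refers to a 95% confidence interval. A t-test of change provides both, and so does a linear model. Mann-Whitney U gives a rank comparison, which is not that difference.

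**The case against.** The strongest reply is that the planned test is sound. The objective is a difference in change, and a t-test of change estimates exactly that. Under randomisation it is unbiased with correct type I error. This stands: the point is about efficiency, and a reader who infers that the planned estimate is biased goes beyond the documents. It is also wrong to say that baseline is not used, since it is subtracted in every change score and enters the paired tests.

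The size of the gain is also open to challenge. The 30-39% for fat mass leans on the intervention arm's fall in SD from 19.1 to 15. The placebo arm gives 10-28%, and equal SDs give 5-25%. The cited patients were more obese than those planned here, so their SDs may not carry over. All of this stands, and the ranges must be reported together.

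A reader might take the cited study's 10.0 kg baseline gap in fat mass (78.2 − 68.2) as a picture of what could happen here. At 65 per arm that gap is 10/2.8 = 3.6 standard errors, so it is not a realistic chance imbalance for this trial. Nor do the documents establish that baseline explains most of that study's 4.0 kg difference. At r = 0.9 with the placebo-arm slope, a 10 kg gap predicts (1 − 0.9 × 11.5/12.0) × 10 = 1.4 kg, about a third.

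Three other inferences lack support. The documents do not show that baseline and surgery type are the strongest covariates. They only imply, through the last secondary objective, that surgery type is recorded. They do not say that the within-group paired tests will be used to judge efficacy.

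A condensed article may leave model details to a fuller plan. Here, however, the article itself fixes the between-group test, the switch rule and the regression covariates.

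**Conclusion.** The concern holds as a matter of precision and of robustness to chance imbalance. The Statistical analysis section fixes an unadjusted comparison of change, and the baseline value of the outcome is never a covariate although it is measured.

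For r between 0.5 and 0.9, adjusting for baseline reduces variance for fat mass by 30-39% (pooled SDs), 10-28% (placebo-arm SDs) or 5-25% (equal SDs). For lean mass the reduction is about 29-44% with the quoted SDs, or 5-25% with equal SDs. A gain appears in every scenario, but its size is uncertain. A one-SE chance gap in baseline fat moves the estimated difference in change by about 0.7-1.6 kg with pooled SDs.

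These figures rest on the assumed r and on the cited study's SDs. They are for fat mass in kg, whereas the Statistical analysis section tests body fat percentage, for which no SDs are given. The statement that the t-test is valid applies to the groups as randomised.

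Separately, the normality switch can replace an estimate of the mean difference in change with a test that does not provide one. The change is worth making, but the plan would not be invalid without it.

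**What to change.** Make the primary between-group analysis a linear model (ANCOVA) of the 6-month value on arm, the baseline value of that outcome, age and gender, with type of surgery added where it is recorded. The change may be used as the dependent variable instead; with baseline in the model, the estimated arm difference is the same. Report the adjusted mean difference with its 95% CI for every outcome.

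Keep Mann-Whitney U as a sensitivity analysis, not as a replacement triggered by a normality pre-test.

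The cost is analysis wording only. The baseline measurements are already scheduled, and no visit or sample is added. Whether surgery type is recorded in the data set should be confirmed before it is named as a covariate.
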